### Treatment fidelity assurance

Fidelity to the therapy program is deemed important as therapists have been shown to demonstrate drift to their own preferred practice of rehabilitation which can introduce variability in outcomes [47]. To help reduce variability attributable to therapists not following the provided rehabilitation protocol, training was provided to a lead therapist at each participating site with a one hour webinar describing the rehabilitation program. These lead therapists serve as a resource for each participating site if questions arise regarding the rehabilitation strategy. Patients who participate in the study may travel from remote locations to the participating surgical sites to receive RTSA. Upon returning to their hometown after surgery, these patients may see therapists other than those at participating sites. In an effort to standardize and optimize fidelity to the formal PT intervention, therapist instruction booklets detailing the rationale of the rehabilitation plan as well as the rehabilitation guidelines are provided to each therapist treating patients in the PT group. The patients in the HT group all receive the same exercise handouts to provide consistency amongst these subjects.

### Participant timeline

Subjects are expected to participate in the trial for a total of two years following the date of surgery. ASES score, pain level, SANE score, and PROMIS-29 v. 2.0 scores are collected preoperatively and at standard of care post-operative appointments at 2 week 6 weeks, 3 months, 6 months, 1, and 2 years. Passive and active range of motion is also collected pre-operatively and at all the post-operative appointments with the exception of the 2 week post-operative appointment. A custom patient questionnaire is administered at every standard of care post-operative appointment. The timeline for variable data collection points is summarized in Table 3. Figure 4 illustrates the study flow including enrollment, interventions, assessment and visits. The decision to terminate the trial rests with the principal investigator.

**Table 3 Tab3:** Outcome measures collected at each timepoint of study

	Pre-op	2 weeks	6 weeks	3 months	6 months	12 months	24 months
**ASES**	Yes	Yes	Yes	Yes	Yes	Yes	yes
**Pain**	Yes	Yes	Yes	Yes	Yes	Yes	yes
**SANE**	Yes	Yes	Yes	Yes	Yes	Yes	yes
**Active ROM**	Yes		Yes	Yes	Yes	Yes	Yes
**Passive ROM**	Yes		Yes	Yes	Yes	Yes	yes
**Study questionnaire**	Yes	Yes	Yes	Yes	Yes	Yes	yes
**Promis 29**	Yes	Yes	Yes	Yes	Yes	Yes	Yes

*ASES* American Shoulder and Elbow Surgery score, *SANE* Single Assessment Numeric Evaluation score, *ROM* range of motion, *Promis 29* Patient-Reported Outcomes Measurement Information System version 2.0

**Fig. 4 Fig4:**
[figure not shown]
Study Flow Diagram

### Statistical analysis

#### Sample size

To determine sample size of this parallel design, the study was powered (a-priori) for the primary outcome measure of the American Shoulder and Elbow Surgeon (ASES) scale at baseline, 2 and 6-weeks, 3 and 6 months post replacement. Study assumptions estimate a 12 month ASES score of 79/100 for the PT group (SD = 15.0) and 69/100 for the HT group (SD = 15.0). The 10 point change is considered a clinically meaningful difference in groups [10].

Assuming normal distributions among the 2 independent group ASES measures, and assuming small-to-medium effect based on between-group differences, we constructed a sample size estimation using a Repeated Measures Analysis of Covariance (ANCOVA). Measuring fixed effects, main effects, and interactions, with an expected 80% power, 6 dedicated time intervals (including baseline), two independent groups, 2 covariates, 1 outcome measure, and a standard error of probability of 0.05, we estimate the need for a minimum sample size of 158 for statistical significance (~ 79 per group). To account for the expected potential 24 crossover (15%) subjects, we will increase enrollment to 182 total. Missing values will be adjusted using a chains equation, multiple imputation method in which we will assign predictor, structural and impute variables.

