## Abstract

**Background:**

Reverse total shoulder arthroplasty (RTSA) has emerged as a successful surgery with expanding indications. Outcomes may be influenced by post-operative rehabilitation; however, there is a dearth of research regarding optimal rehabilitation strategy following RTSA. The primary purpose of this study is to compare patient reported and clinical outcomes after RTSA in two groups: in one group rehabilitation is directed by formal, outpatient clinic-based physical therapists (PT group) as compared to a home therapy group, in which patients are instructed in their rehabilitative exercises by surgeons at post-operative appointments (HT group). Secondary aims include comparisons of complications, cost of care and quality of life between the two groups.

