#### Primary outcomes

The American Shoulder and Elbow Surgeons (ASES) questionnaire is a standardized method of evaluating shoulder pain and function. This instrument is a 100-point scale which assesses pain (50 points) and activities of daily living (50 points), and has demonstrated good reliability/validity following shoulder arthroplasty [38]. The ASES score clinically important change following shoulder arthroplasty is 9 to 10 points [11, 39].

Pain level is monitored using the 0–11 numeric pain rating scale (0 = no pain; 10 = worst pain imaginable) at present, as well as the best and worst rating over the 2 week interval preceding assessment.

The Single Assessment Numeric Evaluation (SANE) score asks a patient the question: “How would you rate your affected joint/region of interest today as a percentage of normal (0% to 100% scale) with 100% being normal?” and has been validated for patients having shoulder arthroplasty [40].

The Patient-Reported Outcomes Measurement Information System (PROMIS-29) version 2 .0 profile assesses pain intensity (0 to 10) as well as seven health domains including physical function, fatigue, pain interference, depressive symptoms, anxiety, social interactions, and sleep disturbance with 4 items per domain. The physical health factor (physical function, pain intensity and interference, and social interactions) and mental health factor (anxiety and depressive symptoms) have been established as valid and reliable [41]. The PROMIS has been determined to be a responsive instrument following RTSA [42].

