#### Data analysis primary outcomes

Study data are collected by clinical research assistants and managed using REDCap electronic data capture tools at the lead institution site (Rush University Medical Center). REDCap (Research Electronic Data Capture) is a secure, web-based software platform designed to support data capture for research studies, providing 1) an intuitive interface for validated data capture; 2) audit trails for tracking data manipulation and export procedures; 3) automated export procedures for seamless data downloads to common statistical packages; and 4) procedures for data integration and interoperability with external sources [36].

Chi square and t-tests will be used to measure differences in baseline characteristics of both groups. Linear mixed effects modeling will be used to measure differences in the outcomes associated with ASES scores, pain, SANE, and range of motion measures across all time points. Linear mixed effects modeling is robust to individual changes, allows for control of variables that are different at baseline, and allows for control of variables that influence outcomes. Linear mixed effects modeling is not bound by the same assumptions as OLS modeling methods (e.g., ANOVA). Differences will be captured for up to 6 time points (pre op to post at 2 and 6 weeks, 3, 6, 12 and 24 months). A *p* value of < 0.05 will be considered statistically significant for all analyses.

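### ASES is the sole primary outcome in the sample size but one of about a dozen in the analysis, all at p < 0.05, and no deciding time point or contrast is named

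*Protocol article*

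**What the plan says.** **Outcome.** The Sample size section of the protocol article calls ASES the primary outcome and counts one outcome measure in the calculation. Elsewhere the primary outcome is plural:

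- The Abstract (Methods) assigns ASES, pain, SANE, and active and passive motion to the primary aim.
- The Primary outcomes section, with its Range of motion subsection, describes ASES, three pain ratings (present, best, worst), SANE, PROMIS-29 and the motion measures.
- The section on data analysis of primary outcomes fits mixed models to ASES, pain, SANE and motion. It plans two sets of analyses for the primary outcomes, plus an as-treated model. Its threshold of p < 0.05 "will be considered statistically significant for all analyses".

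PROMIS-29 is placed inconsistently. It is described under Primary outcomes ("The Patient-Reported Outcomes Measurement Information System (PROMIS-29) version 2 .0 profile assesses pain intensity"), while the Abstract says "Secondary aims include comparisons of complications, cost of care and quality of life between the two groups". The analysis section treats it as secondary.

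**Time.** The Sample size section specifies the ASES "scale at baseline, 2 and 6-weeks, 3 and 6 months post replacement". It continues: "Study assumptions estimate a 12 month ASES score of 79/100". It then enters "6 dedicated time intervals (including baseline" into the calculation. The analysis section says "Differences will be captured for up to 6 time points (pre op to post at 2 and 6 weeks, 3, 6, 12 and 24 months". Table 3 schedules ASES before surgery and at 2 weeks, 6 weeks, 3, 6, 12 and 24 months.

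**The concern.** A superiority trial needs one test, fixed in advance, that decides whether superiority has been shown. Here a reader can take that test to be ASES alone, or any of ASES, pain, SANE and motion. It could fall at 6, 12 or 24 months, or be a comparison over the whole course.

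The hypothesis in the Background is equally broad: better clinical and patient-reported outcomes, faster recovery, and a higher final level. The Discussion says what would follow if the PT group does better, but gives no rule for mixed results across measures.

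At stake is the meaning of a positive result. If one measure at one visit favours PT, the document allows it to be presented as a primary finding at the nominal 5% level, although the real chance of such a finding under no effect is several times higher. A choice made after the results are seen could not be shown to be independent of them.

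**Working it through.** **1. Occasions, side by side**

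| Place | ASES occasions | Count | Last |
|---|---|---|---|
| Sample size, opening list | baseline, 2 wk, 6 wk, 3 mo, 6 mo | 5 | 6 mo |
| Sample size, assumed scores | one | 1 | 12 mo |
| Sample size, model inputs | unspecified, including baseline | 6 | not given |
| Table 3 | pre-op, 2 wk, 6 wk, 3, 6, 12, 24 mo | 7 | 24 mo |

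Adding 12 months to the opening list gives 6, so the count of 6 and the 12-month assumption agree with each other. The opening list is the outlier within the section, and the count of 6 still differs from Table 3.

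**2. Measures in the primary analysis**

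ASES 1 + pain 3 + SANE 1 + motion 7 = 12. Motion is active and passive scaption, ER0 and ER90 (6), plus active internal rotation (1).

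**3. False-positive risk, one test per measure at 0.05, no true effect**

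- Independent tests: 1 − 0.95^12 = 1 − 0.540 = 0.46.
- Equally correlated normal test statistics (200,000 simulated draws; the correlations are assumptions because the document gives none): 0.40 at correlation 0.3, 0.32 at 0.5, 0.23 at 0.7.

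Testing several visits, or choosing among analysis sets, would raise these figures.

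**4. The plan's own sample size, and what a single endpoint needs**

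Inputs from the Sample size section: 79 versus 69, so difference 10; SD 15; power 80%; alpha 0.05 (two-sided assumed); 158 patients, about 79 per group; 24 added for crossover.

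- Crossover addition: 158 × 0.15 = 23.7, taken as 24; 158 + 24 = 182. This reproduces.
- The 158 does not reproduce from 10 points and SD 15. Per group, n = 2 × (1.960 + 0.842)² × 15² / 10² = 2 × 7.849 × 2.25 = 35.3, so 36 (72 in total; 74 by exact t, 73 by ANCOVA with two covariates). Repeated-measures between-group calculations at this effect, with 5 to 7 occasions and assumed correlations of 0.3 to 0.8, give totals of 31 to 62. A total of 158 does appear with a smaller standardised difference of 0.45. This is a separate question about the calculation; here it matters only that 158 is ample for a single ASES contrast.
- Power at 79 per group: standard error = 15 × √(2/79) = 2.387; 10/2.387 = 4.19; 4.19 − 1.96 = 2.23; power 98.7%.
- Allowance for crossover (assumption: 15% of each arm cross at the start and take on the other arm's mean). The difference becomes 10 × (1 − 0.30) = 7 and the variance 225 + 0.15 × 0.85 × 100 = 237.75. Then n = 2 × 7.849 × 237.75 / 49 = 76.2, so 77 per group, still below 79.
- Alternative of keeping all 12 measures co-equal with Bonferroni (0.05/12 each): the ASES effect needs 62 per group, and 79 per group gives 91% power.

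**The case against.** The strongest reply is that the Sample size section does identify ASES as the primary outcome, and that a multiplicity procedure is commonly left to a statistical analysis plan, which is not shown. Both parts are fair, and the absence of a multiplicity method is not the point here. What stands is that other sections of the same article contradict the Sample size section, that the article itself sets 0.05 for every analysis, and that it names no deciding time point or contrast.

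A second reply is that a longitudinal contrast is defensible because speed of recovery is part of the hypothesis. That is true, but the plan does not name that contrast either.

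Four stronger readings are tempting and are not supported:

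- **Twenty primary measures, 64% risk.** Adding the eight PROMIS-29 scores gives 20, and 1 − 0.95^20 = 0.64. But the primary analysis omits PROMIS-29. The Abstract makes it secondary, and the Quality of life and cost analysis section converts five of its domains into one utility compared by one test. Only its placement under Primary outcomes is wrong.
- **The analysis section miscounts its visits.** It mentions up to six time points and names seven occasions, but this can be read as six differences from the pre-operative value, which agrees with Table 3.
- **The effect is diluted by averaging.** Spreading 10 points over seven occasions including baseline would give 10 × 6/7 = 8.6. This presumes an equally weighted group main effect. The plan does not state one, and the sample-size model includes interactions.
- **The groups cannot differ at 2 weeks.** The PT group starts clinic visits 4–5 days after discharge, and half of the ASES score is pain, so an early difference is possible. Only baseline precedes treatment.

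**Conclusion.** The point holds as a contradiction in the document. ASES is the sole primary outcome where the trial is sized and one of several where it is analysed. The occasion list stops before the visit at which the difference is assumed, and no time point or contrast is designated as deciding.

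For the 12 measures in the primary analysis, the chance of at least one false positive is at most 46%, and about 23% to 40% at assumed correlations of 0.7 to 0.3. Even the lower figure is more than four times the nominal 5%. The count of 12 rests on treating each pain rating and each motion separately. The correlations are assumed, and each measure is tested once.

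The matter should be settled before outcome data are analysed by group. The planned size does not stand in the way. The 98.7% power figure assumes complete data and full adherence; the crossover allowance above still fits within 79 per group.

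**What to change.** 1. State one primary endpoint: the PT-HT difference in ASES at 12 months, the only time point with a planning assumption. Estimate it as the 12-month contrast from the mixed model, by intention to treat, with baseline ASES as a covariate.
2. Make pain, SANE, range of motion and PROMIS-29 secondary, with Holm adjustment or an explicit exploratory label. Move PROMIS-29 out of the Primary outcomes section.
3. Correct the occasion list and count in the Sample size section to agree with Table 3: seven ASES occasions, six of them post-operative. Bring the Abstract, the Primary outcomes section and the analysis section into line.
4. Because the trial has commenced, record when the choice was made and that it was made without sight of outcome data by group.

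The cost is an amendment of wording, with no added patients or visits. The downside is that the other measures lose primary status and speed of recovery becomes a secondary question. If the investigators consider speed of recovery the main question, they can name a longitudinal ASES contrast instead, provided that it is single, fully specified and backed by its own planning assumption.

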**Methods:**

This randomised controlled trial has commenced at seven sites across the United States. Data is being collected on 200 subjects by clinical research assistants pre-operatively and post-operatively at 2, 6, and 12 weeks, 6 months, 1 and 2 year visits. The following variables are being assessed: American Shoulder and Elbow Surgeons (ASES), pain level using the numeric pain scale, the Single Assessment Numeric Evaluation (SANE) score, and shoulder active and passive range of motion for analysis of the primary aim. Chi square and t-tests will be used to measure differences in baseline characteristics of both groups. Repeated measures linear mixed effects modeling for measurement of differences will be used for outcomes associated with ASES and SANE and scores, and range of motion measures. Secondary aims will be analyzed for comparison of complications, cost, and quality of life assessment scores using data obtained from the PROMIS 29 v. 2, questionnaires administered at standard of care post-operative visits, and the electronic health record. Subjects will be allowed to crossover between the PT and HT groups, and analysis will include both intention-to-treat including patients who crossed over, and a second with cross-over patients removed, truncated to the time they crossed over.

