### Eligibility criteria/subjects

Participants are identified as potential subjects for this study if they are over 50 years of age, under the care of one of the participating surgeons, and elect to have RTSA for rotator cuff tear arthropathy, massive irreparable rotator cuff tear, or primary osteoarthritis. Subjects are excluded from study participation for the following reasons: history of prior ipsilateral open shoulder surgery, non-reverse total shoulder arthroplasty, RTSA for fracture or revision arthroplasty, RTSA with a tendon transfer, discharge to a skilled nursing facility, in-patient rehabilitation placement, or use of home health therapy prior to progressing in recovery, unwilling to make a good faith effort to adhere to their randomly prescribed rehabilitation scheme, unable to speak, read, or write the English language, have cognitive deficits limiting ability to follow direction, unable or unwilling to be randomised due to financial or personal constraints, or have inability to attend physical therapy (i.e. transportation or financial limitations). Subjects who meet the inclusion criteria are identified at clinical appointments with participating surgeons, and clinical research assistants discuss the study process and review the voluntary informed consent process. At this appointment the following variables are obtained as pre-operative baseline values: American Shoulder and Elbow Surgery (ASES) score, Numeric Pain Rating Scale (NPRS) level, Single Assessment Numeric Evaluation (SANE) score, active range of motion (AROM), passive range of motion (PROM), and Patient-Reported Outcomes Measurement Information System (PROMIS) score. Upon voluntary consent to participate, clinical research assistants employ computer based Research Electronic Database Capture (REDCap) (Nashville, TN) [36] to perform the allocation sequencing of subjects to either the PT or HT group. The randomization schedule is a randomized block design stratified by site using a 1:1 treatment allocation in blocks of size 8.. Patients are encouraged to remain within the group to which they are randomly assigned for the duration of the study, however, if the patient, surgeon, or therapist has concern regarding patient safety, compliance or outcome due to the group assignment, cross-over to the other group will be allowed. The research plan is for approximately a 15% crossover rate based on prior research which planned for 10%, but actually ended up with 30% crossover [37]. The reason for cross-over will be recorded in the electronic health record and reported in the study result.

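### The sample size of 158 at 80% power does not follow from the stated 10-point difference with SD 15, and the effect, time point, target N and treatment of crossover behind it need to be restated consistently

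*Protocol article*

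**What the plan says.** All references are to the protocol article.

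- **Effect.** Sample size: "Study assumptions estimate a 12 month ASES score of 79/100 for the PT group (SD = 15.0) and 69/100 for the HT group", with the same SD of 15 in the HT group. The 10 points are described as clinically meaningful.
- **Effect label.** The next paragraph sizes the trial "assuming small-to-medium effect based on between-group differences" and gives no numerical effect size. The model is a repeated measures ANCOVA with 80% power, alpha 0.05, two groups, two covariates and six time intervals including baseline.
- **Result.** "we estimate the need for a minimum sample size of 158 for statistical significance (~ 79 per group").
- **Visits.** The same section says the trial was powered for ASES "at baseline, 2 and 6-weeks, 3 and 6 months post replacement". That is five occasions, none at 12 months. Table 3 has seven, from pre-op to 24 months.
- **Crossover.** "To account for the expected potential 24 crossover (15%) subjects, we will increase enrollment to 182 total". Eligibility criteria/subjects explains that the planned rate is "based on prior research which planned for 10%, but actually ended up with 30% crossover".
- **Target N.** The abstract's Methods paragraph says "Data is being collected on 200 subjects".
- **Analyses.** Data analysis primary outcomes plans an intention-to-treat (ITT) analysis that keeps crossovers, a second analysis adjusted for crossover, and an as-treated mixed model. The abstract describes the second analysis as removing crossovers, truncated at the time they crossed over.

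**The concern.** The section gives both the assumptions and the answer, so a reader should be able to get from one to the other. A 10-point difference with SD 15 is well above what is usually called small-to-medium, and 158 is about twice what it requires. The 10-point justification and the 158 therefore appear to come from different calculations, and a reader cannot tell which difference, at which visit and on which test, has 80% power.

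This matters for interpretation. The Discussion says that if home therapy does as well as or better than formal PT, it is a convenient and cost-effective strategy. A null result would thus be read in favour of home therapy, so the difference that the ITT analysis could have detected needs to be known. Crossover bears directly on that, and the plan's only allowance for it is extra enrolment.

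**Working it through.** **Inputs.** From the document: difference 79 − 69 = 10; SD 15; power 80%; alpha 0.05; 1:1 allocation; two covariates; N = 158, 182 and 200; crossover 15% planned and 30% in the cited precedent. Assumed: alpha is two-sided (not stated), and the conventional range for small to medium is f = 0.10 to 0.25.

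**1. Effect size.** d = 10/15 = 0.667. For two equal groups f = d/2 = 0.333, which is above the conventional medium value of 0.25.

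**2. N needed for 10 points.** Normal approximation: n per arm = 2 × (1.960 + 0.842)² × 15²/10² = 35.3, so 36 per arm (72). Exact t-test: 36 per arm gives 79.7% and 37 per arm gives 80.8%, so 74 in total.

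**3. Attempt to reproduce 158.** ANCOVA F test with noncentrality f²N and denominator df N − 4 (two groups, two covariates):

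| Numerator df | N for f = 0.333 at 80% | Power at N = 158, f = 0.333 | f giving 80% at N = 158 |
|---|---|---|---|
| 1 | 73 | 98.6% | 0.224 |
| 2 | 90 | 96.9% | 0.249 |
| 5 | 122 | 90.9% | 0.290 |

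A repeated-measures between-group test with six measurements, f = 0.333 and within-subject correlation 0.3 to 0.8 needs 32 to 61. None of these gives 158. Two sets of unstated inputs do give it: f = 0.25 with 2 df (158 gives 80.2%, 157 gives 79.9%), and f = 0.225 with 1 df. The first is what entering a conventional medium effect would produce, but the text states neither the f nor the df.

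**4. What each N detects at 80%.** Two-sample t-test at a single time point, SD 15, no gain from covariates or repeated measures: 6.7 points at 158, 6.3 at 182 and 6.0 at 200.

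**5. The top-up.** 158 × 0.15 = 23.7, taken as 24, and 158 + 24 = 182. This is reproduced. It replaces patients who leave an analysis set. Under ITT they do not leave; they move the group means towards each other.

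**6. ITT power for the stated 10 points.** Worst case: every crossover switches at once and takes the full effect of the other arm. The ITT difference is then 10 × (1 − c_PT − c_HT), where c is the proportion crossing in each arm.

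| Crossover in each arm | ITT difference | Power, N = 182 | Power, N = 200 |
|---|---|---|---|
| 0% | 10.0 | 99.4% | 99.7% |
| 15% | 10 × 0.70 = 7.0 | 87.9% | 90.7% |
| 30% | 10 × 0.40 = 4.0 | 43.2% | 46.7% |

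If 15% cross in one arm only, the difference is 8.5 points and power at 182 is about 97%.

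**7. Visits.** The powered list has five occasions and ends at 6 months; the calculation uses six including baseline; the assumed effect is at 12 months; Data analysis primary outcomes says up to six time points and then lists pre-op plus six post-operative visits.

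**The case against.** The strongest reply is that the error is on the safe side. 158 exceeds what 10 points requires, and an f of 0.25 with 2 df reproduces it exactly, so the likely fault is an unreported, conservative input. That stands as to consequence: the trial is not too small for its stated effect. It does not make the section correct, because the stated inputs and the stated power still disagree.

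A reader might infer that the top-up leaves ITT underpowered. On the plan's own assumptions it does not: power is about 88% for 10 points at 182 with the planned 15%, even in the worst case. It falls below 80% only with much heavier crossover, or for a smaller effect that the document never states.

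A reader might also infer that the 80% describes no analysis the trial will run. The abstract's analysis with crossovers removed is one that the extra 24 do fit. Nor is there a material shortfall: 182 − 24 = 158 by the plan's own count. Taking 15% of 182 instead leaves 154.7, which moves power only from 80.0% to 79.2% at the implied effect of about 6.7 points.

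Choosing 15% when the precedent saw 30% is a planning judgement that the article discloses, so it is no error. The visit counts may be wording slips: six including baseline would run to 12 months, and up to six may mean post-operative visits. That is plausible, but the text has to say so.

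**Conclusion.** The point holds as a fault of derivation and consistency and should be fixed. From 10 points and SD 15, 80% power needs about 74 patients in total. The stated 158 gives about 98.6% (1 df) or 91% (5 df), and small-to-medium does not describe d = 0.67. The time point of the powered effect and the target N (182 or 200) are each stated in conflicting ways.

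The 24 added subjects serve the crossovers-removed analysis and leave ITT dilution uncorrected. ITT power for 10 points at 182 runs from about 99% with no crossover to 88% at 15% and 43% at 30% in each arm.

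These figures rest on a two-sided alpha and, apart from the F-test results, on a single-time-point comparison. The dilution figures also assume an immediate switch with full opposite effect. Later, partial or one-sided crossover dilutes less, and covariate or repeated-measures gains would raise power. The documents do not support a claim that the trial is too small for its stated effect at its planned crossover rate.

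**What to change.** Restate the Sample size section without changing enrolment:

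1. Give one target N, and explain how 158, 182 and 200 relate.
2. Name one effect and time point, the PT minus HT difference in ASES at 12 months, and align the visit list and the count of intervals with it.
3. State the effect size, test, numerator df and within-subject correlation (if used) that produced 158. If these cannot be recovered, give the correct power for 10 points and SD 15. Remove the small-to-medium label or replace it with the number used.
4. Report the detectable difference at 80% power: about 6.7 points at 158, 6.3 at 182 and 6.0 at 200. Label these as single-time-point two-sample values without covariate or repeated-measures gain.
5. Add ITT power for 10 points at 0%, 15% and 30% crossover, with the dilution assumption written out.
6. Say that the added 24 cover only the analysis with crossovers removed.

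The cost is some rewording and one small table. No extra patients are needed. The price is that the table shows openly how far ITT power drops if crossover reaches the precedent's level.
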